** The main indication for acute stroke CTA currently is to determine if the patient is suitable for thrombectomy; such patients are more likely to have a more severe ischaemic stroke and to be younger than the median age of all stroke. CTA is used at some sites prior to thrombolysis but this is not universal and there is no standard or widely agreed practice. There is also less CTA data available in RITeS for testing. We will therefore include all patients for e-CTA testing from all available RITeS trials where CTA was performed routinely at baseline, i.e. we will not select a representative subsample.

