### Secondary outcomes

**
*1. e-ASPECTS processing success and factors influencing accuracy.*
** To present the most complete picture available, we will use the entire RITeS sample for these analyses (i.e. not just the representative sample) but we will also include a sensitivity analysis of the representative sample.

We will report the proportion of scans successfully and unsuccessfully processed by e-ASPECTS and collate reasons cited by e-ASPECTS for any processing failures. We will use summary statistics to describe and compare the subgroups of scans that were successfully versus unsuccessfully processed. This will include patient and radiological factors (see Table 4).

To determine the influence of patient and radiological factors on the accuracy of ASPECTS results produced by e-ASPECTS software, we will perform multivariable ordinal logistic regression using the variables pre-specified in Table 5. The dependent variable will be the absolute difference in ASPECTS between e-ASPECTS and expert human readers (i.e. scalar, 0-10).

For any variables found to be significantly associated with poorer e-ASPECTS results on regression testing (i.e. independently associated with greater difference between e-ASPECTS and expert human reader scores), we will also calculate and compare diagnostic accuracy figures (as above) for each of the subgroup arms (for these analyses only, continuous data will be dichotomised as per Table 5).

Finally, to account for (the as yet unknown) covariates that alter e-ASPECTS diagnostic accuracy figures, we will derive covariate-adjusted ROC curves (AROC)^50^.

**
*2. Identification of CTA obstruction and collateral scoring by e-CTA versus expert human readers.*
** There are two components to the e-CTA output: 1. Where ICA-MCA occlusion is identified, the location is categorised either proximal (ICA/proximal MCA) or distal (distal MCA). Other arteries are not assessed.2. MCA collateral scoring (modified Tan *et. al*. 2009)^51^ is given for all cases on the scale 0 = no collaterals (<10% of affected MCA territory compared to contralateral side), 1 = poor (10–50%), 2 = good (50–90%), 3 = excellent (>90%) collaterals (i.e. includes normal scans).

The expert human rated CTAs available to RITeS include similar scoring methods for comparison with e-CTA outputs, but also additional measures such as degree of arterial patency (i.e. from fully patent through increasingly obstructed to occluded)^22^.

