We will test three components: 1. The proportion of scans where e-CTA and expert humans agree or disagree in the assessment of proximal versus distal ICA-MCA axis occlusion, see Table 6. We will use K-alpha statistics to compare agreement for ICA-MCA axis occlusion detected by e-CTA and expert human readers.2. Diagnostic accuracy of e-CTA for detecting abnormal versus normal intracranial CTA using the methods described above. Abnormal will include both arterial obstruction (partially blocked) and arterial occlusion (completely blocked) for 11 named intracranial arterial segments, i.e. not just ICA or MCA; we will also assess the anterior and posterior cerebral arteries (ACA and PCA, respectively), the vertebral and basilar arteries (five left, five right, one central).3. Agreement on collateral score. Most of the expert collateral scoring available in RiTeS used the Miteff method (three-point scalar = good, moderate, poor)^23^, rather than the modified Tan method (4-point scalar = excellent, good, poor, none) but as ordinal scores, these are comparable. There are three ways to compare the scores (see Table 7). We will test all variations for agreement. We will use K-alpha statistics to check the extent of agreement between e-CTA and human-rated results for the scalar collateral scoring.

**
*3. Repeatability of e-ASPECTS and e-CTA results.*
** We will select a small subgroup of RITeS scans for repeat e-ASPECTS and e-CTA testing. These subgroup sizes were arbitrarily chosen within available time and scan processing resource limitations.

We will include separate assessments of ASPECTS (n=100), haemorrhage detection (n=20) and CTA scoring (n=20). We will select scans for repeat testing, blind to all previous results (from e-ASPECTS, e-CTA or expert human readers) except knowledge of previous successful processing by e-ASPECTS or e-CTA. To ensure this subsample remains largely representative of the available stroke trial mix, we will use cluster random sampling, as follows. Each stroke trial represents a cluster. Random samples will be drawn from each cluster in numbers to match individual stroke trial proportions in the entire representative sample until the total numbers required are reached for each of the separate assessment groups, total n=140.

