### 2c. Association between e-ASPECTS or e-CTA results and clinical outcome after stroke

We will use the entire RITeS samples of NECT and CTA for these analyses but also perform sensitivity analyses using the representative NECT sample.

In separate multivariable analyses, we will test whether the three main software outputs of e-ASPECTS (ASPECTS result) and e-CTA (ICA-MCA axis occlusion, MCA territory collateral score) are independently associated with stroke outcome. We will include the following variables in each model since these are already known to be associated with outcome after stroke: age, NIHSS, time from stroke onset, treatment with alteplase and/or thrombectomy (vs no treatment). The dependent variable in each model will be functional outcome after stroke. Assessment of functional outcome after stroke varies among the RITeS trials and includes either the modified Rankin Score (mRS) at 90 days, or the Oxford Handicap Scale (OHS) at 6 months from stroke onset. Both mRS and OHS are 7-point scalar ranging from normal (0) through increasing disability (1–5), to death (6). We will use multivariable ordinal logistic regression to calculate common odds ratios for good outcome, presented as per Table 10.

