**TOTAL**			

**Note:** All results n (%). Proximal = ICA or proximal MCA (M1). Distal = distal MCA (M2+).

**Table 7. T7:** Options for comparing modified Tan (e-CTA) and Miteff methods (human rated) of MCA collateral scoring.

Modified Tan used by e-CTA to grade collaterals	Miteff comparison 1	Miteff comparison 2	Miteff comparison 3
3 = Excellent (>90%)	Good	Good	Good
2 = Good (50–90%)		Moderate	Moderate
1 = Poor (10–50%)	Moderate		Poor
0 = None (0–10%)	Poor	Poor	

**Table 8. T8:** Planned results for e-ASPECTS and e-CTA repeatability testing.

Tested Component	Result
e-ASPECTS, ischaemia	N, % with matched ASPECTS results
	N, % for each of 1–10 point ASPECTS difference
	Median, IQR for difference in scores
e-ASPECTS, haemorrhage	N, % with matched location results
	N, % for each of 22 named regions
	Median, IQR for comparison of haemorrhage volumes
e-CTA, obstruction	N, % with matched ICA-MCA proximal vs distal results
e-CTA, collateral scoring	N, % with matched collateral scores
	Median, IQR for comparison of collateral scores

Note: ICA = internal carotid artery. MCA = middle cerebral artery.

**Table 9. T9:** Planned results for effect of e-ASPECTS on diagnostic confidence and treatment decisions questionnaire.

Question	Total, n (%)	Subgroups: e-ASPECTS overlay, reader experience, visible ischaemic lesion, haemorrhage, hyperattenuating arteries, leukoaraiosis, atrophy, old stroke lesions		Absolute differences, 95% CI and p-value
		With n (%)	Without n (%)	
Found e-ASPECTS overlay helpful				
Decision				
Treat patient with thrombolysis/ thrombectomy				
No acute treatment				
Request further radiological input				
Confidence in decision				
Very unsure				
Unsure				
Sure				
Very sure				

Note: Table truncated for presentation of subgroups.

**Table 10. T10:** Planned ordinal regression analysis results with 3–6-month post-stroke outcome as dependent variable.

Variable	Raw Data N (%) or Median (IQR)	Odds Ratio, OR	95% Confidence Interval	p-value
Age, years				
NIHSS				
Time from stroke onset, minutes				
Treated with alteplase +/- thrombectomy				
Software-derived result *				

Note: NIHSS = National Institutes of Health Stroke Scale, IQR = Inter-quartile range. * Either ASPECTS result, presence/absence of ICA-MCA axis occlusion, MCA collateral score.

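### Collateral analyses pool normal scans with well-collateralised occlusions, so the 2c outcome association could reflect occlusion status alone, and so could the agreement result if experts graded patent scans

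*SAP article*

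**What the plan says.** All references are to the SAP article.

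- **What e-CTA returns.** Under Secondary outcomes, item 2, the collateral score "is given for all cases on the scale 0 = no collaterals" upwards, and the top grade is "3 = excellent (>90%) collaterals (i.e. includes normal scans". The grades are defined relative to the affected MCA territory.
- **Who is analysed.** Under Inclusion and exclusion criteria (sample for e-CTA evaluation): "We will therefore include all patients for e-CTA testing from all available RITeS trials where CTA was performed routinely at baseline". No subsample is drawn.
- **Agreement.** Component 3 of the same secondary outcome says: "We will use K-alpha statistics to check the extent of agreement between e-CTA and human-rated results for the scalar collateral scoring". On the human side: "Most of the expert collateral scoring available in RiTeS used the Miteff method (three-point scalar = good, moderate, poor". Table 7 gives three ways to align the scales. Grade 3 aligns with good in all three, and there is no row for a patent axis.
- **Outcome.** Section 2c says: "We will use the entire RITeS samples of NECT and CTA for these analyses". Its only sensitivity analysis concerns the representative NECT sample. The covariates are age, NIHSS, onset time and treatment. The three software outputs go into separate models, and the note to Table 10 lists the software result as "Either ASPECTS result, presence/absence of ICA-MCA axis occlusion, MCA collateral score".

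No section restricts the collateral analyses to occlusions or adjusts them for occlusion. The plan also does not say whether experts scored collaterals on patent CTAs.

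**The concern.** A collateral grade describes filling beyond a blockage. Grade 3 here holds two different groups: patients with no occlusion, and patients with an occlusion and excellent filling. If the lower grades come mainly from occluded patients (an assumption, though a natural one given the grade definitions), the score is partly an occlusion indicator.

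Two results could then mislead. In 2c, the score could be reported as independently associated with outcome although the grading among occluded patients carries no information. In the agreement analysis, pairs in which both sides call a normal scan normal could raise K-alpha and hide poor agreement in the patients for whom the grade matters.

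**Working it through.** The plan gives no sample size, power or agreement figure for these analyses, so there is nothing to reproduce. The check asks what the planned analyses return when collateral grading is uninformative by construction.

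**Inputs from Table 1.** Baseline CTAs: IST-3 about 270, PISTE 65, PRACTISE 50% of 271 ≈ 136, SITS Open 5% of 293 ≈ 15. Sum: 270 + 65 + 136 + 15 = 486, taken as about 485. POSH lists patency on CTA but no CTA count. Including all 113 of its patients would give 599.

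**Assumed inputs (not in the documents).** Occlusion prevalence 30-100% for agreement and 40-45% for outcome. e-CTA grades 0/1/2/3 among occlusions 15/30/35/20%. Expert poor/moderate/good 30/35/35%. Residual occlusion odds ratio (OR) for worse outcome 1.0 to 3.0 after the planned covariates.

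**Outcome model, by arithmetic.** Suppose grade has no effect within occlusions. Its coefficient in the planned model is then approximately the slope of occlusion on grade times ln(occlusion OR), ignoring the other covariates.

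- Mean grade: occluded 0.30×1 + 0.35×2 + 0.20×3 = 1.6; normal 3.
- Variance within occlusions: (0.30×1 + 0.35×4 + 0.20×9) − 1.6² = 3.5 − 2.56 = 0.94.
- At 40% occlusion: covariance −0.4×0.6×1.4 = −0.336; grade variance 0.4×0.94 + 0.4×0.6×1.4² = 0.846; slope −0.336/0.846 = −0.397.
- OR per grade for good outcome, exp(0.397 × ln OR): 1.17 at 1.5, 1.32 at 2, 1.44 at 2.5.

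Simulation of the proportional-odds model with NIHSS included, at 40% occlusion, gives 1.17 to 1.44 over the same range, which agrees.

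**Outcome model, share of simulated analyses with p<0.05** (n = 485, no collateral effect within occlusions):

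| Residual occlusion OR | Planned model | Occlusions only |
|---|---|---|
| 1.0 | 2% | 6% |
| 1.5 | 28-37% | about 3-8% |
| 2.0 | 75-80% | about 2-8% |
| 2.5 | 87-93% | about 3-8% |
| 3.0 | 99% | 3% |

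The ranges come from separate runs at 40% or 45% occlusion. The 1.0 and 3.0 rows are from the 45% run only, with 100 replicates. Adding occlusion as a covariate in that run gave 1-6% and an OR per grade of 0.99 to 1.02. A weaker residual effect (OR 0.8 for good outcome, i.e. 1/0.8 = 1.25 for worse) gave 15%. With 200 usable CTAs the rate falls to 17-63% for ORs of 1.5 to 2.5, but the OR per grade stays at 1.18 to 1.45.

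**Agreement.** Let e-CTA and expert grades be independent among occlusions. Under comparison 1 of Table 7, chance raw agreement is 0.15×0.30 + 0.30×0.35 + 0.55×0.35 = 0.34. Suppose a share p of scans is normal and both sides give them the top grade. Raw agreement becomes p + (1 − p)×0.34, which is 0.67 at p = 0.5 and 0.80 at p = 0.7. Ordinal K-alpha by simulation, across the three Table 7 comparisons:

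| Share normal | Perfect separation by software | 90% of occlusions, 95% of normals correctly separated |
|---|---|---|
| 0% | −0.05 to 0.00 | −0.06 to 0.00 |
| 30% | 0.22-0.40 | 0.18-0.34 |
| 50% | 0.35-0.54 | 0.28-0.46 |
| 70% | 0.43-0.63 | 0.37-0.54 |

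On the Landis and Koch bands that the plan adopts, no real agreement could be labelled anything from slight to substantial. With a modest true relation (latent correlation 0.5) and perfect separation, K-alpha moves from 0.32-0.36 in occlusions alone to 0.57-0.71 at 50% normal.

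**The case against.** A reader might infer that the plan necessarily manufactures both agreement and an outcome association. The documents do not support that.

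- **Agreement is conditional.** Inflation requires experts to have graded patent CTAs, and as good. The plan does not say they did. The only statement on when readers score collaterals concerns the tertiary timing study, where it is done when relevant. If experts scored only occlusions, patent scans have no human pair and leave the K-alpha. That is close to the restriction recommended here. This stands, and it leaves the agreement part as an unfixed analysis set, not a demonstrated bias.
- **The outcome effect is conditional.** NIHSS, age, time and treatment are in the model. If they absorb the effect of occlusion, false findings stay near nominal. The documents give no residual OR. This stands too, and is why the weaker cases are shown.
- **The sample may be smaller.** Processing failures, missing outcomes and the routine-CTA condition could all reduce 485. That lowers the rejection rates but leaves the biased estimate.
- **The target is the software output.** The tertiary outcome asks whether e-CTA results relate to outcome. For that question a score that includes normals is the thing tested, and its association is real. It would still not show that grading collaterals adds anything to knowing whether an artery is blocked, so the problem is one of interpretation.

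The plan also states the grade 3 definition openly and tests occlusion separately. Neither removes the mixing in the collateral analyses.

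**Conclusion.** The point holds in conditional form. As written, 2c cannot separate a collateral effect from an occlusion effect, so an independent association could come from occlusion status alone. With about 485 CTAs and about 40% occluded, the chance of p<0.05 with worthless grading is roughly 30-40%, 75-80% and about 90% at residual occlusion ORs of 1.5, 2 and 2.5. It is near nominal if occlusion has no effect beyond the covariates. This part does not depend on how experts handled normal scans.

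For agreement, zero agreement among occlusions could show as a K-alpha of about 0.2-0.6, depending on the Table 7 comparison, occlusion prevalence and software accuracy, and only if experts graded patent scans as good. Prevalence, grade mix and effect sizes are all assumptions. No primary outcome is touched.

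**What to change.** 1. State that the collateral agreement analysis (component 3) and the 2c collateral model apply to patients with expert-rated ICA-MCA occlusion. Experts already rated arterial patency, so no new reading is needed.
2. If an all-case 2c model is kept as a test of the raw software output, add occlusion status as a covariate or code no occlusion as its own category.
3. Report separately the normal scans that e-CTA graded below 3.

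The cost is SAP wording and precision. At 40% occlusion, 0.40 × 485 = 194 scans remain. With the grade mix above, the standard error for grade grows by about √[(485 × 0.846)/(194 × 0.94)] ≈ 1.5. Little real information is lost, because normal scans that all sit at grade 3 say nothing about the effect of grade among occlusions.

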### Secondary outcomes

1. Proportion of scans successfully versus unsuccessfully processed by e-ASPECTS (i.e. where ASPECTS results are provided or not provided), factors associated with e-ASPECTS processing success and result accuracy.2. Proportion of ICA-MCA occlusion versus normal ICA-MCA axis correctly identified by e-CTA, accuracy of e-CTA for detecting any intracranial obstruction, difference in CTA collateral scores provided by e-CTA versus expert human readers.3. Repeatability of e-ASPECTS and e-CTA results on a subset of scans presented twice.

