**Table 3. T3:** Planned assessment of radiological characteristics of the entire RITeS dataset.

Radiological Finding		N (%) or Median (IQR)
Ischaemic brain changes	None	
	Subtle (e.g. loss of grey-white margins)	
	Obvious (e.g. hypoattenuation relative to normal white matter +/- swelling)	
Ischaemic location	MCA territory	
	Other cerebral	
	Brainstem or cerebellum	
	Cortical	
	Subcortical	
Hyperattenuating arteries	List location	
Haemorrhage location	Deep	
	Lobar	
	Intraventricular	
	Extra-axial	
Structural stroke mimic	List type (e.g. tumour, inflammation, collection)	
Pre-stroke brain changes	Atrophy	
	Leukoaraiosis	
	Old Stroke lesions	
CT slice thickness	Thin (≤ 1 mm)	
	Medium (> 1 mm ≤ 5 mm)	
	Thick (> 5 mm)	

**Table 4. T4:** Planned univariable comparison of scans successfully versus unsuccessfully processed by e-ASPECTS.

Variable	Successfully Processed	Not Successfully Processed	Absolute differences, 95% CI and p-value
Patient age (median, IQR)			
Patient sex (n, %)			
Minutes from stroke onset to scan (median, IQR)			
NIHSS (median, IQR)			
Stroke aetiology (n, %): • Ischaemia MCA territory • Ischaemia elsewhere • Haemorrhage • Mimic			
Presence of pre-stroke brain changes (n, %): • Atrophy • Leukoaraiosis • Old stroke lesions			
CT slice thickness (n, %): • ≤ 1 mm • > 1 mm ≤ 5 mm • > 5 mm			
Image quality (n, %): • Good quality • Movement artefacts • Streak artefacts • Patient malposition			

Note: IQR = Inter-quartile range. MCA = middle cerebral artery. NIHSS = National Institutes of Health Stroke Scale.

**Table 5. T5:** Variables for multivariable analysis and subgroups for diagnostic accuracy testing.

Clinical Characteristics		Imaging Findings		Imaging Technique	
Age	≤60 years	ASPECTS	<6	CT slice thickness	≤1 mm
	>60 years		≥6		> 1 mm
NIHSS	0–6	Infarct Location	MCA territory	Poor patient positioning	Yes No
	7–12		Elsewhere		
	>12	Atrophy, Leukoaraiosis, Old stroke lesion	Yes No		
Time from stroke onset to scan	<3 hours				
	3+ hours			Imaging artefact (movement or streak)	
Knowledge of affected side	Yes No				

**Table 6. T6:** Comparison of ICA-MCA axis occlusion identified by e-CTA and expert-human groups.

Human Readers e-CTA	Proximal Occlusion	Distal Occlusion	TOTAL
Proximal Occlusion			
Distal Occlusion			

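### Table 6, the analysis written for e-CTA detection of ICA-MCA occlusion, has no category for no occlusion and so cannot deliver the outcome of occlusion versus normal axis

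*SAP article*

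**What the plan says.** In the Methods, item 2 of the secondary outcomes lists separate e-CTA targets. The first is the "Proportion of ICA-MCA occlusion versus normal ICA-MCA axis correctly identified by e-CTA". The second is the "accuracy of e-CTA for detecting any intracranial obstruction". The third concerns collateral scores.

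In the Statistical analysis, the section on CTA obstruction and collateral scoring sets out three components:

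- **Component 1:** the share of scans on which software and readers "agree or disagree in the assessment of proximal versus distal ICA-MCA axis occlusion, see Table 6". The next sentence adds: "We will use K-alpha statistics to compare agreement for ICA-MCA axis occlusion detected by e-CTA and expert human readers".
- **Component 2:** diagnostic accuracy for abnormal versus normal CTA over 11 named arterial segments, with partial obstruction counted as abnormal.
- **Component 3:** collateral scores.

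Table 6 is titled "Comparison of ICA-MCA axis occlusion identified by e-CTA and expert-human groups". Each of its axes has Proximal Occlusion, Distal Occlusion and TOTAL, and its note defines only the proximal and distal categories.

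The same section says that e-CTA assigns a location only once it has found an ICA-MCA occlusion, and that "Other arteries are not assessed".

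**The concern.** The first listed outcome is a detection question: is the axis occluded or not? The analysis written in its place is a location question: given an occlusion, is it proximal or distal? Followed as written, Table 6 tests location labelling among scans on which software and expert already agree that there is an occlusion.

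The SAP's introduction describes the CTA assessment as a tool to detect large vessel obstruction, and says CTA is used to identify patients suitable for thrombectomy. For that use, the errors of interest are occlusions the software misses and occlusions it reports that are not there. Table 6 has no cell for either. A reader of the results could take good agreement in that table as evidence of good detection.

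**Working it through.** The SAP gives no sample size, power or expected agreement for the CTA analyses, so there is no figure to reproduce. The check is structural, with an illustration of size.

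**Outcome against analysis**

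| Listed outcome | Analysis written for it | Does it answer the outcome? |
|---|---|---|
| ICA-MCA occlusion versus normal axis | Component 1, Table 6: proximal versus distal | No: no category for a non-occluded axis |
| Any intracranial obstruction | Component 2: 11 segments, partial or complete | Yes |
| Collateral scores | Component 3, Table 7 | Not at issue here |

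The two-category layout is not damage from text extraction. The sentence citing Table 6, its rows and columns, and its note all agree. Table 8 uses the same proximal-versus-distal wording for repeatability.

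The third category exists elsewhere in the plan. The analysis principles define the CTA result as occlusion or no occlusion. Tertiary outcome 2b samples CTAs from no-obstruction, proximal and distal strata. The note to Table 10 uses presence or absence of ICA-MCA occlusion. The e-CTA sample takes all patients from trials with routine baseline CTA and does not require an occlusion.

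**Illustration: inputs.** From Table 1, the CTA count is about 270 (IST-3) + 65 (PISTE) + 0.5 × 271 (PRACTISE) + 0.05 × 293 (SITS Open) = 485. POSH is left out because its CTA number is not given. It is also unclear whether IST-3 and SITS Open meet the condition of routine baseline CTA. I use a round 500. All else is assumed: half the scans occluded (250), 50-70% of occlusions proximal, 90% location agreement when both call an occlusion, and false positives split equally between locations.

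**Formulas.** Nominal K-alpha = 1 − Do/De. Do is the observed proportion of disagreement. De = 1 − Σ n_c(n_c − 1) / [n(n − 1)], where n_c counts the ratings in category c from both raters and n is the total number of ratings.

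**Worked case** (70% proximal; detection 85% proximal and 50% distal; 10% false positives):

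- Jointly called occluded: 175 × 0.85 + 75 × 0.50 = 148.75 + 37.5 = 186.25. These alone enter Table 6.
- Location disagreements: 0.10 × 186.25 = 18.6.
- Missed: 26.25 + 37.5 = 63.75. False: 250 × 0.10 = 25.
- All disagreements: 18.6 + 63.75 + 25 = 107.4. Table 6 shows 18.6 of them, so 83% are absent.
- K-alpha, 2x2: Do = 0.100, De = 0.3565, giving 0.72.
- K-alpha, 3x3: Do = 2 × 107.4 / 1000 = 0.2147, De = 0.5861, giving 0.63.

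**All four scenarios, at 50% and at 70% proximal:**

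| False positive; proximal; distal detection | Shown / all disagreements, 50% | K-alpha 2x2 / 3x3, 50% | Shown / all disagreements, 70% | K-alpha 2x2 / 3x3, 70% |
|---|---|---|---|---|
| 5%; 90%; 60% | 19 / 94 | 0.79 / 0.69 | 20 / 80 | 0.73 / 0.73 |
| 10%; 85%; 50% | 17 / 123 | 0.79 / 0.58 | 19 / 107 | 0.72 / 0.63 |
| 20%; 80%; 50% | 16 / 154 | 0.79 / 0.49 | 18 / 140 | 0.73 / 0.53 |
| 10%; 70%; 30% | 13 / 163 | 0.77 / 0.42 | 15 / 145 | 0.68 / 0.48 |

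**A second check** uses 485 scans, 70% of occlusions proximal, and equal sensitivity for both locations. Prevalence runs over 30-70%, sensitivity over 50-90% and specificity over 80-95%. The 2x2 K-alpha is 0.77 in every case, while the 3x3 value runs from 0.29 to 0.80. The Table 6 layout does not respond to detection performance at all under these conditions.

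**The case against.** A reader might infer that ICA-MCA detection is never analysed, or that the plan offers no sensitivity or specificity for it. The document does not support that, for three reasons.

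1. **General rule.** The analysis principles make diagnostic accuracy the principal method wherever it can be applied, with experts as reference and Wilson intervals, and define the e-CTA result as occlusion or no occlusion. Together with the outcome list, this implies an ICA-MCA 2x2 by default. That stands. But the section that specifies the e-CTA analyses applies diagnostic accuracy only to component 2, so for this outcome the analysis has to be inferred.
2. **K-alpha.** The K-alpha sentence does not cite Table 6 and could mean occlusion detected, yes or no. That also stands, so one cannot assert that K-alpha will be conditional on joint detection. The categories are nevertheless not fixed, and chance-corrected agreement is not a proportion correctly identified.
3. **Component 2.** A missed ICA-MCA occlusion is a false negative there if e-CTA calls the scan normal, and a false occlusion on a normal CTA is a false positive. So detection errors are absent from Table 6, not from the plan. But component 2 also counts as false negatives the abnormalities in arteries that e-CTA does not assess. It can credit a false ICA-MCA call as correct when another artery is abnormal. Accuracy for the axis cannot be recovered from it.

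The illustration can also be challenged: its rates have no basis in the documents, and its K-alpha values shift with the assumed proximal share. It shows what the layout can hide and predicts nothing about e-CTA.

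**Conclusion.** The mismatch is real and rests on the text alone. A named secondary outcome, occlusion versus normal ICA-MCA axis, is paired with a table that cannot show missed occlusions, false occlusions or correctly normal scans. Component 2, the K-alpha sentence and the general rule each soften the gap, but none fixes an axis-specific result.

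Under the stated assumptions, Table 6 would show about 13-20 of 80-163 disagreements, so roughly 75-92% would be absent. K-alpha would be 0.68-0.79 on the 2x2 against 0.42-0.73 on the 3x3. In the best-detection scenario at 70% proximal the two coincide at 0.73, and in the second check the 3x3 value can slightly exceed the 2x2. The direction and size of the K-alpha difference are therefore not general. The absence of detection errors from the table is.

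The plan should be changed, but this concerns a secondary outcome and leaves the primary e-ASPECTS analyses untouched.

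**What to change.** - Redraw Table 6 as a 3x3: none, proximal, distal, for e-CTA against expert.
- State that K-alpha for ICA-MCA occlusion is computed on those three categories.
- Add sensitivity, specificity and positive and negative predictive values, with Wilson 95% confidence intervals, for ICA-MCA occlusion versus no ICA-MCA occlusion. Say where expert-rated partial obstruction of the axis falls in that split.
- Keep the 11-segment analysis beside it. Which of the two leads is the authors' choice, since the outcome list does not rank them.
- Align the obstruction row of Table 8 with the same three categories.

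The cost is one table redrawn, one extra 2x2 and a small edit to Table 8. No new scans or readings are needed.
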